**Study sites/locations**

The study will be conducted concurrently in both Blantyre and Lilongwe districts, the two biggest cities in Malawi. It will target health workers employed in various health facilities (private, public or mission-managed/religiously affiliated) both within the urban and peri-urban area of both districts.

**Study participants**

Study participants will be recruited from all primary, secondary and tertiary care facilities within Blantyre and Lilongwe districts.

Inclusion criteria are as follows:

- Type of service provider (cadre)
- English language fluency
- Smartphone ownership
- No or current CBT for mild or moderate mental health disorders
- No suicidal ideation
- Initial mental health test scores below severe levels

The participants of this study will be health workers of the following professional cadres from health facilities:

| - Doctors | - Nurses |
| --- | --- |
| - Medical Assistants | - Clinical officers |
| - Laboratory technicians | - Physiotherapy technicians |
| - Pharmacists |  |

The minimum required educational qualification is a diploma in their respective fields of specialization, in adherence to the Ministry of Health employment criteria for the respective cadres of health workers. However, Medical Assistants who completed 2 years of college will be allowed to participate even though their qualification is a certificate. These selection specifications are put in place based on the general assumption that such participants are competent in the English language as a medium of communication, which will facilitate their interactions with the Vitalk App and the mental health resource website since all the interactions on these platforms are in English. Additionally, study participants are expected to own a smartphone on which they can download and use the Vitalk App and access the mental health resource website, which is an additional reason for limiting participant selection to the above cadres.

Exclusion criteria for this study includes all other hospital- or health-related personnel, such as health surveillance assistants, hospital assistants or laboratory assistants, due to their lower educational qualification requirement for employment. In addition, considering that smart phones are not very widely available within many social circles in Malawi and are considered to many as a luxury, this research assumes that cadres listed above have a higher chance of owning a smart phone due to their higher grade of pay than those of lower employment cadres.

Lastly, a clinical exclusion criteria will apply to all health workers currently under treatment for a severe mental disorder and to all study applicants with severe symptoms of depression, anxiety or burnout according to their initial scores from standard mental health tests. These conditions will include suicidal ideation. Those excluded will not have their identity revealed, but they will simply not be able to stay registered for the study. Participant meeting the exclusion criteria will be offered resources for self-help and contacts of mental health counselors.

**Study period**

[figure not shown]
*Figure 2. Study process and timeline*

This trial is scheduled to span 56 calendar days, from the week beginning on the 4^th^ of October 2021 until the 26^th^ of November 2021. The entire process and timeline are shown in Figure 2. Study participants in both the treatment and control groups will begin their participation in this project by attending a half-day workshop prior to the start of the trial before October 4, which shall serve a dual purpose. Firstly, during this workshop participants shall receive a presentation about general tenets of mental health, how mental health affects work performance, the impact of one’s mental health upon their work, and a description of the four specific areas of mental health that will be assessed: namely anxiety, depression, resilience, and burnout. Secondly, participants will be provided with an overview over the study of ‘*an online self-help for mental wellbeing*’ and the eligibility criteria, but NO specifics about interventions in the treatment or control groups will be mentioned. Only information pertaining to both groups will be discussed.

At the workshop, participants will have the option to join the trial or to leave. Those opting to join will be directed to the study web-portal, provide their consent, complete a pre-screening to establish eligibility, and register for the trial. All participants eligible at this stage shall then complete the initial mental health assessment to assess the initial scores for depression, anxiety, resilience, and burnout. Anybody scoring at the severe level for any of the four scales or showing signs of suicidal ideation will be excluded from the trial and be provided with contacts to mental health professionals in Malawi and Vitalk-affiliated psychologists. All participants passing these final eligibility criteria shall be admitted to the trial and familiarized with links to mental wellbeing resources on the internet and contacts with local psychologists and mental health counselors.

To achieve some degree of participant blinding to the intervention NO information about Vitalk or specifics about interventions in the treatment and control groups will be shared with workshop participants. Participants who completed registration will NOT be informed of their admission into the trial during the workshop; this will happen through an email after the workshop that provides the links to either Vitalk for the treatment group or the website for the control group or informs those not eligible for the trial. The trial manager will monitor whether the desired sample size is achieved; if it is not, additional recruitment efforts and workshops may be necessary.

Participants in the treatment group will receive daily messages and counseling for the first four weeks of the trial to encourage engagement with Viki, the Vitalk virtual counselor. This will change to every other day during weeks five though eight. Participants in the treatment and control group will receive weekly emails throughout the trial to encourage use of web mental health resources. Both groups will be asked to use the mood meter at least once a week to monitor mood changes. Those self-identifying with extreme negative emotions will be offered to take a relevant standard test again and encouraged to seek professional help.

All participants will be asked to take the standard mental health tests again in week four or five of the trial. This will be done virtually though email to all trial participants as a mid-trial check-in. After the end of the 56-day period, in week nine, both the treatment and control groups will be invited to attend a concluding half-day workshop, during which they shall again be evaluated on their general mental health using the previously completed mental health assessment tools. They shall then complete an anonymous online questionnaire on their experiences of interacting with the app or accessing the referred mental health links. Some participants will be invited to take part in focus group discussions (FGD) aimed at gaining detailed feedback about their experiences of using the two different interventions and the Vitalk app specifically (treatment group participants only for the latter). A mix of in-person and anonymous virtual FGDs are planned given the sensitive nature of mental health. A virtual FGD would be done without video and participants would only be identified by number not name. The use of two FGD formats, in-person and virtual, allows the comparison of how responses may differ between these two approaches. This study concludes with the workshop and FGDs in the 9^th^-week.

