4.1. Study Design, Randomization, And Blinding

This study is guided by the conceptual framework shown in Figure 1 below. The study is a two-arm, parallel randomized controlled trial with a pre-treatment assessment, 8-week intervention period and mid-study assessments at 4-5 weeks and an end-of-study assessment at 9 weeks^^[[1]](#footnote-1)^^. Interested study participants will be randomly assigned to either the treatment or control group at the time of registration. Vitalk, the developer of the app, will create a study web portal where study participants register, give their consent, are assigned to one of the study arms, are given a unique study identification number, and enter their demographic information. Depending on the random assignment, participants will be taken to either the treatment app, Vitalk, or the website for the control group. This is a single blinded design because only the research team will be blinded to the study arm assignments; all participants in both study arms will be told they are participating in ‘*an online self-help for mental wellbeing*’.

[figure not shown]

*Figure 1. Study framework*

Participants will be required to seek approval from their employers to participate in the study, because some activities will occur during working hours, but no information collected during the trial that could identify participants or their facilities of affiliation will be shared with the employers. A trial manager, someone appointed by Vitalk and the Department of Psychology (UNIMA) who is not part of the research team, will provide technical support in case participants encounter difficulties with the study portal or the Vitalk app and be therefore privy to the group assignment, but this information will not be shared with the research team during the study. The study portal and control group website will be optimized for and accessible through smartphones. Vitalk is a smartphone app for Android and iOS.

- 1. Treatment and control group interventions
[figure not shown]

     1. Vitalk chatbot app (treatment group, *active*)

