Originating from Brazil, Vitalk is an automated chatbot delivering mental health content to its users using a conversational format, with the aim of improving well-being by reducing stress, anxiety and depression using a preventative approach to mental health (Daley, Hungerbuehler et al., 2020). The Vitalk app uses psychoeducation, cognitive restructuring, behavioral activation, gratitude, and practical exercises (such as breathing, relaxation and meditation) to bring about improvements in users’ mental health (ibid). These techniques and strategies are rooted in CBT and Positive Psychology, two commonly used psychotherapy methodologies that have been used widely in various settings and have registered high effectiveness among patients presenting with various psychological challenges (Beck, 2011; Seligman, 1998; Wills, 2009). Only the treatment arm of the study will have access to Vitalk.

- - 1. Mental health resource website (control group, *passive*)

The control arm of the study will have access to a website with links to mental health resources from WHO and other self-help providers as well as contact information for psychologists and mental health counselors in Malawi. This website consists of a few pages with basic mental health and coping information, links to mental wellbeing resources, mood meter and standardized mental health tests. Its content is static without user interaction beyond clicks to access web-based
[figure not shown]
mental health resources. Whether or not these resources are used depends entirely on the initiative of control group participants.

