**Risks**

Vitalk is not intended to replace a mental health professional or to offer treatment. Users are made aware of this in the informed consent that each participant is required to sign. Study participants are advised to seek additional support if they show a high risk of depression, anxiety, or stress during the study. Where Vitalk identifies a risk issue, the user is sent details of support services, including the national suicide line, and, if the participant elects the option, a follow up conversation with a healthcare professional from Vitalk who is not affiliated with the study is initiated. Participants identified as high risk or with suicidal tendencies will be removed from the study and referred for mental health support. Under no circumstances will the participant’s identity be shared with the research team or anybody outside this study.

The Vitalk App, the mental health resource website and all literature and presentations shared with the research participants shall contain contact information of mental health service providers that the research participants may access in the event of needing further psychological support.

We expect minimal risks to study participants due to COVID-19. The risk of exposure that may be encountered during the workshops is significantly mitigated by the fact that the majority of health workers are vaccinated against COVID-19. Regardless of this, both the research team and participants will be required to maintain the recommended amount of social distance, wear face masks and follow local guidelines as stipulated by the ministry of health.

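### No stated step turns a severe score at the week 4–5 or week 9 tests into the referral that the Risks section intends

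*Combined protocol and SAP*

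**What the plan says.** The Study period section sets a clear rule at entry: a severe score on any of the four scales, or signs of suicidal ideation, leads to exclusion and to contacts for professional help. It then repeats the tests in both arms. On the mid-trial round it says "All participants will be asked to take the standard mental health tests again in week four or five of the trial", and the same tools are used once more at the concluding workshop in week 9.

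The Risks section holds the response. It says "Study participants are advised to seek additional support if they show a high risk of depression, anxiety, or stress during the study" and "Participants identified as high risk or with suicidal tendencies will be removed from the study and referred for mental health support". The one detection step it describes begins "Where Vitalk identifies a risk issue, the user is sent details of support services, including the national suicide line", followed by an optional conversation with a professional from Vitalk.

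On the two interventions the protocol says "Only the treatment arm of the study will have access to Vitalk". The control website offers "links to mental wellbeing resources, mood meter and standardized mental health tests", and of that site it says "Its content is static without user interaction beyond clicks".

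**The concern.** The sponsor already treats these scores as something to act on, because they decide entry. The same scores are collected twice more, on the study's own platforms and in both arms, and nothing says what happens if one is severe. The Risks section intends that people at high risk are referred, but a rule with no stated trigger cannot be applied consistently.

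This is first a matter of participant safety. Week 9 is the weakest point, because the study ends there and no later test or prompt follows. A secondary matter is that if detection differed between arms, removals could differ too, and with them the pattern of missing outcome data.

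**Working it through.** No power or precision figure is in question. The check sets the safety steps side by side and then makes three small counts.

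**Steps compared**

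1. Baseline (Study participants; Study period). Trigger: severe score or suicidal ideation. Action: exclusion and contacts.
2. Week 4–5 by email and week 9 at the workshop (Study period). Same instruments, both arms. Trigger, action and responsible role: none stated.
3. Mood meter (Study period). Both arms, weekly. Trigger: the participant reports extreme negative emotions. Action: a retest is offered and seeking help is encouraged. No rule attaches to the retest score.
4. Risks section. Action: removal and referral, with no restriction by arm. Trigger: no instrument, score or time. Named identifier: Vitalk.
5. Data analysis method. In-trial monitoring by the trial manager covers arm sizes and whether data are complete and appropriate. Section 4.1 blinds the research team. Nobody is assigned to read an individual score for safety.
6. Annex 1.2.3 shows that scores are captured on both platforms. Annex 1.2.1, question 7, asks about suicidal thoughts at screening. Neither Annex 1.2.3 nor the Study period section says how that criterion is read at follow-up.

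Item 2 has data but no trigger, item 4 has an action but no trigger, and nothing joins them.

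**Counts**

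- Rounds: baseline, week 4–5 and week 9 make 3. A score rule is stated for 1, so 3 − 1 = 2 have none.
- People (Sampling method): 640 × (1 − 0.20) = 512 per arm, and 512 × (1 − 0.75) = 128 with final data. Both reproduce the plan's figures. Attendance per round is not given, so up to 512 control participants would be invited at each.
- Severe share at follow-up: not in the documents. As an assumption only, 1%, 3% and 5% of 512 are 5.1, 15.4 and 25.6 people; of 128 they are 1.3, 3.8 and 6.4.
- Gap to the next scheduled test, from the 4 October start: week 4 opens on 25 October, week 5 closes on 7 November, and week 9 runs from 29 November to 5 December. The shortest gap is 7 to 29 November, 22 days. The longest is 25 October to 5 December, 41 days. The mood meter runs until the 56 days end. (The Data management section puts the concluding workshop in week seven, which cannot follow a 56-day period; I use week nine.)

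**The case against.** The strongest reply is that the protection is there and only the wording is loose. The Risks section speaks of high risk of depression and anxiety, which PHQ-9 and GAD-7 measure, and the baseline rule already fixes severe as the safety level. The follow-up assessment may itself carry the suicidal-ideation criterion, since the baseline section lists that criterion after the initial tests as well as in pre-screening. The limit on interim use sits under data analysis, and an automatic message is neither sharing nor analysis. All this is fair, and it makes the remedy cheap. It does not supply the missing trigger.

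Three stronger readings are tempting, and the documents do not support them.

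- A reader might infer that there is no in-trial safety response, or that Vitalk is the only detection step. Neither is so. The advice and the removal rule cover all participants, provider contacts reach both arms, and the mood-meter prompt is a second step that includes controls.
- A reader might infer that detection exists in the treatment arm alone. That needs Vitalk to mean the app. Section 4.1 also says "Vitalk, the developer of the app, will create a study web portal where study participants register", the Risks section refers to a professional from Vitalk, and it speaks of users when describing the consent that every participant signs. The text is ambiguous.
- A reader might infer a bias of known size in favour of Vitalk. Unequal removal is possible, but the share removed and their scores are not given. The 1.5 points in the sample-size section are a paired pre-post difference, so a gap in score level cannot be set against them. The planned mixed model also keeps earlier scores.

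Figure 2 and the consent pages could not be seen, and either might hold a rule.

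**Conclusion.** The point stands in a limited form: the response exists, but no available text ties the repeat tests to it. Followed as written, a severe score at week 4–5 or week 9 triggers no referral. This is plainest for a control participant, whose website is static and whose in-trial prompt depends on recognising and reporting extreme distress. Two of the three rounds are affected. The number of people cannot be derived from the documents; the 1% to 5% range above is illustrative, and the conclusion does not depend on it. Unequal removal by arm is a possibility only, with no size attached. The sponsor should correct this, and confidence is medium because of the unseen figure and consent pages.

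**What to change.** Amend the Study period and Risks sections as follows.

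- **Trigger.** On submission at both follow-up rounds and at any mood-meter retest, apply automatically and identically in both arms: GAD-7 of 15 or more, PHQ-9 of 20 or more, and the suicidal-ideation criterion. Name the item that carries that criterion, and repeat Annex 1.2.1 question 7 only if the existing assessment does not carry it. State whether the OLBI high cut-off (2.68 or above) also counts, because the Study participants section excludes severe burnout.
- **Response.** Show an immediate on-screen message with support contacts and offer an opt-in referral to the professionals already named in the Study period and Risks sections. Opt-in respects the promise not to share identity. At week 9 removal no longer matters, but referral does.
- **Handling.** Make flags visible only to the trial manager, so that the research team stays blinded. State that a flag counts as identification of high risk, record any removals by arm, and keep scores already collected in the analysis.

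The cost is a small added function on a website now described as static and possibly one extra question per round. The trial manager, whose stated duties are technical support and data monitoring, would also forward opted-in referrals, without clinical judgement. No new visits are needed.

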**Specific research objectives**

In addition to testing the null hypothesis, this study intends to achieve the following specific objectives:

1. To evaluate whether the levels of engagement and continuity of use of Vitalk are adequate to meet the need for mental health support (rate of adoption and continuity).

2. To explore whether the frequency and duration of interaction with Vitalk are significant predictors of mental health outcomes (stickiness/intensity of use).

3. To establish whether the use of Vitalk significantly reduces the number and duration of sub-clinical and clinical episodes of depression, anxiety, resilience, and burnout over the study period (effectiveness).

4. To discover which features of Vitalk are liked or disliked; what improvements are suggested by users; and whether user experience drive stickiness (user experience).

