**Sampling method**

Study participants will be recruited from all primary, secondary and tertiary care facilities within Blantyre district on a first come-first served basis. While this is a convenience sample based on self-selection, random assignment to treatment and control groups will counteract biases inherent to this approach. All participants are volunteers and agree to be assigned to either the treatment or the control group.

The required study population size for paired tests of correlated means was calculated using STATA 17 and is based on the following:

- Pre-post-treatment difference of 1.5 points on standard test scales
- Standard deviation of the difference = 6
- Power 80%
- Significance level 5%

This results in a minimum of 128 participants per study arm. Given the continuity experience – the proportion of participants completing the pre- and post-treatment assessments for depression, anxiety and stress – of 20-45% reported by Daley, Hungerbuehler et al. (2020), we assume that the dropout rate will be as high as 75% for at least one of the standard mental health assessments. This means that a sample of 512 participants will be required per study arm to yield an effective post intervention sample of 128. Furthermore, if 20% of potential study participants will not meet inclusion criteria or drop out for other reasons, about 640 people will need to be recruited initially per study arm. Therefore, the total number of participants for this study is 1280.

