**Thank you!**

Annex 1.2.5

**FOCUS GROUP DISCUSSION GUIDE: TREATMENT GROUP**

**CLOSING WORKSHOP ON PSYCHOSOCIAL WELLBEING FOR HEALTHWORKERS**

**DATES:**

**VENUE:**

**OBJECTIVE:** This qualitative enquiry seeks feedback from the experiences of health workers who had been interacted with the Vitalk App over 56 days as a digital mental health solution aimed at improving on their mental health.

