**QUESTIONS:**

1. What are some of the common mental health challenges that health workers face?
2. What specific/unique mental health challenges have health workers faced due to the COVID-19 pandemic?
3. How do social norms or attitudes affect people’s ability to get psychosocial help or counselling?
4. What was your initial expectation of the HRH2030 workshops for the psychosocial wellbeing of health workers?
5. What has your experience of using the Vitalk app been like during the past month?
6. How have you been using the Vitalk app in your everyday life?
7. What did you find enjoyable about the conversations with Viki?
8. What conversations with Viki did you find the most helpful?
9. What conversations with Viki did you find the least helpful?
10. What are the main benefits that you got from using the Vitalk app?
11. Which mental health recommendations did you learn from Viki that you will continue to use from now onwards?
12. How would you explain Vitalk to a person who doesn’t know about it?
13. What challenges did you face (if any) in using the app?
14. For the participants who did not use the app consistently, what was the reason for the inconsistency?
15. How do you think the Vitalk app can be improved to make it more engaging and effective?

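### Stated experience and reasons for low use are collected only through instruments tied to the closing workshop, so participants who do not return have no described route to inform objective 4

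*Combined protocol and SAP*

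**What the plan says.** The fourth aim under Specific research objectives is: "To discover which features of Vitalk are liked or disliked; what improvements are suggested by users; and whether user experience drive stickiness (user experience".

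Study period describes two instruments that ask for it, both in week nine.

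- **Questionnaire.** The protocol says that "both the treatment and control groups will be invited to attend a concluding half-day workshop". After repeating the standard tests there, "They shall then complete an anonymous online questionnaire on their experiences of interacting with the app or accessing the referred mental health links". The forms are Annex 1.2.4 (treatment) and Annex 1.2.6 (control). Each asks for days of use, with a zero-days option, and then asks those below 20 days why they did not use it more.
- **Focus groups.** "Some participants will be invited to take part in focus group discussions (FGD) aimed at gaining detailed feedback about their experiences". On format: "A mix of in-person and anonymous virtual FGDs are planned given the sensitive nature of mental health". The treatment guide (Annex 1.2.5) is headed "CLOSING WORKSHOP ON PSYCHOSOCIAL WELLBEING FOR HEALTHWORKERS" and asks: "For the participants who did not use the app consistently, what was the reason for the inconsistency". The control guide (Annex 1.2.7) has a near-identical heading and a matching question about the website.

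Data management method also attaches the questionnaire and the focus-group guide to the concluding workshops. It places them in week seven, although after the 56 days; that should be reconciled with Study period.

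On expected losses, Sampling method says: "we assume that the dropout rate will be as high as 75% for at least one of the standard mental health assessments".

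**The concern.** Whether experience drives continued use is a question about the whole range of engagement, including people who lost interest early. If reasons and opinions come only from those who return in week nine, the disengaged end of that range is likely to be thin. The helpfulness rating, the recommendation score, the listed benefits and the reasons for low use would then describe attenders, while a reader may take them to describe everyone given the app.

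The mixed model in Data analysis method deals with the mental health scores. The plan says nothing about non-response on objective 4, and names no denominator for it.

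**Working it through.** **Step 1. Who is asked, when, and what.**

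| Source | Reaches people who miss the workshop? | Asks experience or reasons? |
|---|---|---|
| Mid-trial email, week four or five (Study period) | Yes, sent to all | No, standard tests only |
| Use logs (Annex 1.2.3) | Yes | No; they record content opened, usage, internet gaps and support requests |
| Closing questionnaires (Annexes 1.2.4, 1.2.6) | No route described | Yes |
| Focus groups (Annexes 1.2.5, 1.2.7) | Not stated; guides carry the workshop heading, some sessions are virtual | Yes, from some participants |

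No exit question, withdrawal-reason form or follow-up of non-attenders appears in the text. The consent pages and the timeline figure were not available for this check, so an item there cannot be ruled out.

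**Step 2. Reproduce the plan's retention figures (Sampling method).** Inputs: difference 1.5, SD of the difference 6, power 80%, significance level 5% (taken as two-sided, which reproduces the figure).

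- Normal approximation: (6 × (1.960 + 0.842) / 1.5)² = 125.6, so 126. The paired t calculation gives 128 (power 0.8015), as stated.
- 128 / (1 − 0.75) = 512 per arm.
- 512 / (1 − 0.20) = 640 per arm, and 2 × 640 = 1280.
- Implied retention: 128 / 512 = 25%, leaving 512 − 128 = 384 per arm without post-intervention data.

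**Step 3. Use it as a proxy for attendance.** The plan gives no attendance rate. The post-treatment tests are taken at the workshop just before the questionnaire, so the share completing them is a rough stand-in. The earlier Vitalk study cited in Sampling method had 20–45% completing both assessments. Treating 20%, 25% and 45% as attendance is an assumption.

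**Step 4. What the unasked could change.** Let *a* be the share of admitted participants who answer and *p* the share of them giving a particular answer. Among all admitted, the share lies between *a·p* and *a·p* + (1 − *a*), so the width is 1 − *a* whatever *p* is. The last column takes *p* = 20% (say, disliking a feature) purely as an example; the documents give no such figure.

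| Assumed *a* | Asked per arm | Not asked per arm | Width | Range if *p* = 20% |
|---|---|---|---|---|
| 20% | 512 × 0.20 ≈ 102 | ≈ 410 | 80 points | 4% to 84% |
| 25% | 128 | 384 | 75 points | 5% to 80% |
| 45% | 512 × 0.45 ≈ 230 | ≈ 282 | 55 points | 9% to 64% |

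These are extreme bounds. They show how little the attenders' answers constrain the figure for all admitted. They do not estimate a bias.

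**The case against.** The strongest reply is that the plan does ask people who stopped. Invitations go to both arms whatever their use, the form offers zero days, low users are asked why, and the focus groups ask inconsistent users. This stands. A reader might infer that those who quit the app are never asked why, but the documents contradict that: stopping the app and missing the workshop are different things. Respondents are selected for attending, not for continued use. Because days of use and opinions are on the same form, their relation can still be examined among respondents, though selection may distort it.

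Second, a reader might take 25% as planned attendance. It is not. It is a worst case about completing the tests, used to inflate the sample size. Someone missing one scale could count as a dropout and still fill in the questionnaire. Benefits/Impacts also provides $10, a lunch allowance and, at the final workshop, airtime, any of which may raise turnout.

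Third, a reader might infer that satisfaction will be overstated. That is plausible, but the documents do not show it: health workers could miss a half-day event because of shifts rather than dislike.

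Fourth, the virtual focus groups are not expressly limited to attenders. That is an ambiguity to settle. Even if open to others, they cover only some participants and give no denominator.

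Finally, the focus-group part is exploratory, with interpretative phenomenological analysis as its main method, and does not aim at a prevalence. That lowers the stakes but leaves the questionnaire ratings and the question about continued use exposed.

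**Conclusion.** The point holds in a limited form. Participants absent in week nine have no described route to state their experience or their reasons, so the answers to objective 4 are likely to under-represent the disengaged. On the plan's worst-case assumption, used as a rough proxy for attendance, that is up to 384 of 512 admitted per arm. Over the cited 20–45% range it is about 282 to 410. Actual attendance may be better, and the documents fix neither the size nor the direction of any resulting bias.

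This is a weakness in a stated secondary aim that is cheap to reduce. The main treatment comparison is untouched. The verdict rests on the available text containing no exit or withdrawal-reason item.

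**What to change.** 1. In week nine, have the trial manager email the existing arm-specific online questionnaire to every admitted participant who did not complete it at the workshop. Because the form is anonymous, the attendance list can serve to identify them; alternatively, send it to all with an instruction to complete it once. Plan this in advance, since Data management method keeps contact details only during the trial phase.
2. State whether non-attenders may join the virtual focus groups, and offer some of those places to non-attenders and low users.
3. Report responses against all admitted per arm, split by the days-of-use item already on the form.
4. Do not use separate links based on the use logs. Annexes 1.2.4 and 1.2.6 promise that answers will not be tied to the respondent, and such links would attach logged use status to them.

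The cost is one emailed link per arm and some redirected invitations. No new instrument is needed, and the trial already emails all participants weekly and at mid-trial. The downsides are a likely low response among non-attenders and a mix of workshop and remote completion, both of which should be reported.
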